### ***Analysis of ALSFRS-R***

Our primary analysis strategy is to use the “shared parameter” model described in Vonesh, Greene and Schluchter, 2006 [148]. They propose a random effects analysis of variance to model

the change in ALSFRS-R over time. The basic idea of this model is that each subject has his or her own trajectory with a random slope, intercept and curvature, the average value of which may depend on treatment. The primary analysis of ALSFRS-R will include measurements made during the first 12 months only, to minimize the effect of drop out. They extend this model to include a parametric model for mortality during the 12 month period that we are analyzing. This corrects the estimate of the treatment effect for loss of data which might be dependent on the subject's ALSFRS-R trajectory. We will model survival by assuming that the mortality distribution is Weibull with a scale parameter that depends on the random slope and intercept of ALSFRS-R. We plan to continue follow up of subjects who discontinue treatment so that we should have ALSFRS-R at all of the time-points on the vast majority of subjects except for those that die. As a sensitivity analysis, we will also correct for subjects who are missing their final ALSFRS-R measurements using a modification of the model described above. This model can be modified by having two causes of "failure", death and "missing further data". Then both of these outcomes can be modeled using a Weibull model as above and the difference in the slopes due to treatment can be calculated, corrected for dropouts and deaths which may be associated with ALSFRS-R.

The primary analysis will use a p-value of 0.05. There will be no efficacy stopping boundaries for ALSFRS-R. We don't include an efficacy stopping boundary for ALSFRS-R because if ALSFRS-R is strongly positive it will indicate that with enough follow up and subject accrual we may eventually see a survival benefit. Since measuring the survival benefit, if there is one, is a primary goal of the trial we would not want to stop the trial if there is a good chance of seeing a survival benefit. Futility boundaries are described below. With the sample size of 600 subjects and a 2:1 randomization we will have 80% power to see a 25% decrease in the rate of ALSFRS-R decline in either treatment group.

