**Randomization**

Approximately 60 eligible subjects from up to 12 clinical centers will be randomized (1:1:1) in STAGE 1 to ceftriaxone 2 grams per day, 4 grams per day, or color-matched placebo. All STAGE 1 subjects will participate in a pharmacokinetic study seven days after starting study treatment and then proceed into STAGE 2 in the same treatment arm assignment. Once data from STAGE 2 is analyzed and a decision is made on final dosage and treatment schedule for the STAGE 3 efficacy trial, the STAGE 1 subjects assigned to the placebo arm will continue on placebo; and the STAGE 1 subjects assigned to ceftriaxone (2 grams or 4 grams/day) will be

reassigned to the ultimate ceftriaxone dosage chosen for the efficacy trial (STAGE 3). The additional 540 subjects entering STAGE 3 will be randomized (2:1) to ceftriaxone or matched placebo. The randomization will be stratified by clinical site and riluzole use. Randomization will be blocked to ensure that the treatment groups are balanced within a site after a certain number of subjects have been enrolled at that site.

---

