## 2 BACKGROUND AND SIGNIFICANCE

### 2.1 Background and Rationale

#### 2.1.1 *Clinical Features and Epidemiology of ALS*

Amyotrophic lateral sclerosis is a rare degenerative disorder of large motor neurons of the cerebral cortex, brain stem and spinal cord that results in progressive wasting and paralysis of voluntary muscles [7]. The incidence of ALS is currently approximately 2/100,000/year [8, 9] and may be increasing [10]. The lifetime ALS risk is 1 in 600 to 1 in 1000. Even though the incidence of ALS is similar to that of multiple sclerosis [11], the prevalence is only 4-6/100,000 (about 25,000 patients in the United States), due to the higher mortality rate. Fifty percent of ALS cases die within three years of onset of symptoms and 90% die within five years [11]. The median age of onset is 55 years. The cause in most cases is unknown. Age and gender are the only risk factors repeatedly documented in epidemiological studies [12]. There is a slight male predominance (3:2 male to female ratio) in sporadic ALS. No treatment

prevents, halts or reverses the disease, although riluzole use is associated with a slight prolongation of survival [13, 14].

The majority of ALS cases are sporadic (SALS); 10% are familial (FALS). More than 100 point mutations in the gene encoding cytosolic copper-zinc superoxide dismutase (SOD1) have been demonstrated to cause typical FALS [15]. Essential features of ALS are progressive signs and symptoms of lower motor neuron dysfunction (atrophy, cramps, and fasciculations) associated with corticospinal tract signs (spasticity, enhanced and pathological reflexes) in the absence of sensory findings [9]. There is relative sparing of muscles of eye movement and the urinary sphincters. The course is relentless with decline in strength, respiratory function and overall function with time during the active phase of the disease [16]. Natural history studies have determined that age at onset, site of onset, delay from first symptom to entering ALS clinic, and rate of change in respiratory function are significant covariates of survival [17-20]. No study has correlated activity of any surrogate marker with the extent of motor neuron loss as detected by post-mortem examination.

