## 4. SUBJECT SELECTION AND ENROLLMENT

### 4.1 Inclusion Criteria

1. Participants with familial or sporadic ALS diagnosed as laboratory supported probable, probable or definite according to the World Federation of Neurology El Escorial criteria [142], Appendix 2
2. Age 18 years or older
3. Capable of providing informed consent and complying with trial procedures.
4. Vital capacity (VC) at least 60% predicted value for gender, height and age at screening
5. Women must not be able to become pregnant (e.g. post menopausal, surgically sterile, or using adequate birth control methods) for the duration of the study. Adequate

- contraception includes: abstinence, hormonal contraception (oral contraception, implanted contraception, injected contraception or other hormonal (patch or contraceptive ring, for example) contraception), intrauterine device (IUD) in place for  $\geq 3$  months, barrier method in conjunction with spermicide, or another adequate method (as determined by steering committee member review). Women of childbearing potential must have a negative pregnancy test at screening and be non-lactating.
6. First ALS symptoms occurred no more than 3 years prior to screening visit
  7. Not taking riluzole, or on a stable dosage for at least thirty days prior to the screening visit
  8. Subject has a competent caregiver who can and will be responsible for administration of study drug. If there is no caregiver, another qualified individual must be available to administer the study drug.
  9. Geographic accessibility to the study site
  10. Subjects medically able to undergo placement of central venous catheter as determined by the investigator (to include absence of systemic infection, a medical disorder which precludes catheter placement)

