#### **STAGE 3**

**Primary Outcome measures.** Co-primary outcome measures include survival, defined as time to death, tracheostomy or the initiation of permanent assisted ventilation (PAV) and change in function as measured by ALSFRS-R. Non-invasive ventilation techniques utilized for more than 22 hours daily for more than one week will be the criterion for determining PAV. The primary analysis will be by "intention to treat." We will ascertain the status of all subjects at the end of the study and every subject will be included in the analysis whether or not they elected to stop treatment before the end of the study. The analysis of survival will use a log-rank test stratified by riluzole use. The use of the log-rank test and a design where everyone is treated until the end of the study has several advantages over treating everyone for only 52 weeks and using the 52-week mortality. By enrolling subjects at a constant rate in over an approximate 24-month enrollment period, we will be able to follow subjects anywhere from 12-36 months, with an average of 18 months of on-treatment follow-up. This is close to estimated median survival time found in previous ALS studies [95]. The power of tests comparing survival distributions depends on the number of events during the trial. Thus there are substantial power advantages

for treating people for a longer duration. To examine the co-primary endpoints jointly, our primary analysis strategy is to use the “shared parameter” model described in Vonesh, Greene and Schluchter[148]. This is described in more detail below in Section 9.1.3. The data analysis will be based on the ALSFRS-R during the first 12 months of treatment.

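### The co-primary ALSFRS-R model names no term for riluzole or for any screening predictor of progression, so an inexpensive gain in precision is forgone; its size depends on a predictive strength the documents do not give.

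*Combined protocol and SAP*

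**What the plan says.** Section 9.1.3, Analysis of ALSFRS-R, is the only specification of this co-primary model. In it, "each subject has his or her own trajectory with a random slope, intercept and curvature, the average value of which may depend on treatment". Death is handled jointly: "We will model survival by assuming that the mortality distribution is Weibull with a scale parameter that depends on the random slope and intercept". Only measurements from the first 12 months are used. No riluzole term, site term or screening covariate is named in either part.

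On power, for 600 subjects allocated 2:1, the same section states: "we will have 80% power to see a 25% decrease in the rate of ALSFRS-R decline in either treatment group".

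Elsewhere the protocol treats these variables as relevant:

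- Précis, Randomization: "The randomization will be stratified by clinical site and riluzole use". Section 4.3.4 also has riluzole as a stratum.
- Section 6.3.4, STAGE 3, and Section 9.1.3 analyse survival with a "log-rank test stratified by riluzole use".
- Section 2.1.1 lists "age at onset, site of onset, delay from first symptom to entering ALS clinic" and the rate of respiratory change as covariates of survival.
- Section 4.1 makes timing of onset an entry criterion: "First ALS symptoms occurred no more than 3 years prior to screening visit".
- Section 6.2.1 has vital capacity (VC) and ALSFRS-R measured at screening.
- Section 6.3.4 does not stratify for age at diagnosis or site of onset and relies on randomisation for balance.

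**The concern.** The two co-primary endpoints are given equal emphasis, yet the riluzole stratum enters one primary analysis and not the other. More importantly for precision, nothing known at screening is allowed to predict how fast a subject will decline. Randomisation balances such variables on average, but balance does not remove the variation they explain from the error term. Only terms in the model do that.

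The ALSFRS-R test carries weight beyond its own claim. Its p-value is half of the futility rule, and it can become the sole primary endpoint if too many subjects stop treatment. Precision here is worth having if it costs little.

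**Working it through.** **Inputs.** 600 subjects at 2:1: Stage 1 gives 40 active and 20 placebo, and the further 540 give 360 and 180, so 400 against 200. Power is 80% for a 25% slowing. Alpha is 0.05; sidedness is not stated for ALSFRS-R, and two-sided is assumed. Section 6.3.4 gives a placebo decline of 0.92 units/month (SE 0.08), from an earlier trial and on the ALSFRS, not the ALSFRS-R. The documents give neither the SD of slopes nor the number of placebo patients behind that SE.

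**The plan's 80%.** It cannot be reproduced, only inverted.

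- Difference: 0.25 × 0.92 = 0.23 units/month.
- Standard error needed: 0.23 / (1.960 + 0.842) = 0.0821.
- Implied slope SD: 0.0821 / √(1/400 + 1/200) = 0.0821 / 0.0866 = 0.948 units/month, about 103% of the mean decline. A one-sided 0.05 test would imply 1.07.
- The quoted SE implies an SD of 0.08 × √n. That equals 0.948 only if n was about 140, which cannot be checked.

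So 80% is neither confirmed nor refuted.

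**Effect of covariates.** If they explain a share R² of the slope variance, the standard error shrinks by √(1 − R²), and

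power = Φ(2.8016 / √(1 − R²) − 1.960).

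This scales from the stated 80% and does not depend on the 0.92. R² is an assumption throughout.

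| R² (assumed) | Power | Detectable slowing, 25% × √(1 − R²) | N for 80% power, about 600 × (1 − R²) |
|---|---|---|---|
| 0 | 80.0% | 25.0% | 600 |
| 5% | 82.0% | 24.4% | 570 |
| 10% | 84.0% | 23.7% | 540 |
| 20% | 88.0% | 22.4% | 480 |
| 25% | 89.9% | 21.7% | 450 |

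Reaching 85% power needs R² of about 12.6%.

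**Riluzole alone.** With 60% users (the figure in Section 4.2) and slopes differing by a fraction g of 0.92, R² = 0.6 × 0.4 × (0.92g)² / 0.948². For g = 10% this is 0.2% and power is 80.1%; for g = 25% it is 1.4% and power is 80.6%. Even g = 30% gives only 80.8%.

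**Is slope variance mostly between subjects?** A generalised least squares check used the protocol's visits (screening, weeks 4, 16, 24, 32, 40, 48), an assumed residual SD of 2.0 and an assumed intercept SD of 5.5. Measurement error is then about 4% of the slope variance (0.039 / 0.899), and power is 83.8% and 87.6% at R² of 10% and 20%. The protocol's own information formula points the same way: at 0.75 per subject plus 0.25 per subject-year, halving follow-up from a year to six months lowers information only from 1 to 0.875.

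**What the screening score already captures.** In the same check, with no covariates, an intercept common to both arms and an intercept–slope correlation of 0.2 or 0.4 give 80.9% or 84.6%. With an arm-specific intercept the score adds nothing. Section 9.1.3 sets a common intercept for the secondary outcomes but does not say which applies to ALSFRS-R.

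**The case against.** The strongest reply is that nothing here is an error. The 80% is stated for the model as written, the unadjusted contrast is valid under randomisation, and leaving out a stratum makes the standard error, if anything, slightly too large. That stands.

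The size of the gain is also assumed. Section 2.1.1 names covariates of survival, not of ALSFRS-R slope. Section 3.1 links ALSFRS-R closely to survival but gives no figure for how well any screening variable predicts slope. That stands too, which is why only a range is given.

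Riluzole is weak as a source of power: Section 2.1.6 reports longer survival with it but no better strength. Its inclusion rests on consistency. Site is also a stratum, but with 600 subjects at about 70 centres (8 to 9 each) and a survival test that omits site as well, no site term is proposed.

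The ALSFRS-R paragraph offers only an outline of the model, so covariates are unstated rather than excluded. This is fair, but a primary model should be settled before unblinding.

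Two technical objections change the remedy. First, if the Weibull scale uses deviations from the fitted mean, moving predictable slope into fixed effects takes it out of the death model and could weaken the correction for informative loss. Second, a pre-study decline rate, (48 − screening score) / months since first symptom, reuses the score that is already the first response. Any onset-based covariate also needs a recorded date, which the entry criterion implies but the listed screening procedures do not state.

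**Conclusion.** The omission is real, and the direction is certain for any R² above zero: precision is forgone. At assumed R² of 5% to 25%, power would be about 82% to 90% instead of 80%, less the part already captured through the screening score. Almost all of this would come from the screening predictors; riluzole contributes under one point for slope differences up to 30%.

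A reader might infer that the trial is underpowered for ALSFRS-R or that the 80% is overstated. The documents do not support that: they give no slope SD, and the 80% appears to be for the model without covariates. Nor do they support reading the omission as bias, or as a material loss of power from leaving out riluzole. This is a worthwhile improvement to the plan, not a defect in its validity.

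**What to change.** In Section 9.1.3, before unblinding:

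- Add riluzole and riluzole-by-time to the longitudinal part, with a short fixed list of screening covariates: age, screening VC and time since first symptom, each as a main effect and an interaction with time.
- Enter the same covariates in the Weibull part, so that the correction for informative death is kept.
- Confirm that the onset date is recorded. Use a pre-study decline rate only if it is, and then state how its overlap with the screening ALSFRS-R response is handled.
- State whether the intercept is common to both arms.
- Keep treatment-by-time as the test, and report the model without covariates as a sensitivity analysis.
- Report the slope SD behind the 80%.

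The cost is SAP wording, a few more parameters in both parts of the model, and a rule for occasional missing onset dates. No new visit is needed.

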### ***Stopping for Futility in STAGE III***

Stopping for futility could occur if the trial doesn't reach accrual targets or if both ALSFRS-R and survival do not show sufficient trends towards efficacy. In addition if the dropout rate is so high that the power to show a survival benefit is minimal, then the primary endpoint of the trial will be changed to compare 12 month changes in ALSFRS-R and subjects will be given the option of discontinuing study medication at 12 months.

**Accrual Targets:** The study should take five months to begin fully accruing at a rate of 25 subjects per month. If the study does not reach at least 60% of its accrual goal at any interim analysis then the study will have reached an accrual futility boundary. At this point the DSMB can stop the study for accrual.

**Efficacy Targets:** Both Survival and the slope of ALSFRS-R will be used to determine a futility stopping boundary. The trial will be considered futile if both ALSFRS-R and fail to cross the futility boundary specified by a beta spending function  $.05 * t$ . The table below shows the p-value targets (one sided p-values) for these measures. For an endpoint such as ALSFRS-R, it cannot be defined as the proportion of subjects that have entered the trial because some subjects may not have more than a few ALSFRS-R measurements. Its formal definition is the ratio of the variance of the treatment time interaction at the final analysis over the variance at the interim analysis.

The information time for the ALSFRS-R is assumed to be proportional to .75 times the number of subjects plus .25 times the number of subject years of follow up. This was calculated by a linear regression of the variance of the efficacy parameter on various combinations of sample size and follow up period.

**Treatment Discontinuation Rate Targets:** All analyses will be by “intent to treat”, but the effect of subjects’ discontinuation will be to reduce the power of the study as the treatment effect will be diminished by subjects in the treatment group who don’t continue treatment. This effect will be largest in the survival comparison and will have a minor effect on ALSFRS-R which is only used for the first year to judge efficacy. The hazard ratio used in the power calculation is an “intent to treat” hazard ratio, it reflects the hazard ratio achieved by an effective treatment on all participants combined whether or not they are completely compliant and are treated for the whole period. The “as treated” hazard ratio, the hazard ratio achieved by an effective treatment if all patients are completely compliant, would need to be higher than the “intent to treat” hazard ratio. The relationship of the two hazard ratios does not only depend on the number of subjects that discontinue treatment but on when they discontinue. In the simplest model, described below, it depends on the proportion of time that subjects are treated. If the dropout rate does not meet the treatment discontinuation target that subjects are treated significantly less than 2/3 of the time the recommendation would be to use ALSFRS-R as the primary endpoint and only follow each subject for one year. Survival data would still be collected but would not be expected to be impacted significantly by treatment. The following paragraphs give a justification of this target.

Under a Poisson event model, the primary effect of treatment discontinuation can be measured by the ratio,  $p$ , of the follow up that a patient is on treatment divided by their total follow up. . If  $p$  is the proportion of time that a subjects is on treatment divided by the total time they are included in the study, then the “intent to treat” hazard ratio will be approximate  $1/(p/R+(1-p))$  where  $R$  is the on-treatment hazard ratio (Placebo/RX) . The parameter  $p$  will be estimated by the sum of the area under the time to discontinuation curves for each subject’s potential follow up divided by the sum of the area under the time to death curve. To project the value of  $p$  for the entire study it is necessary to know these beyond the current follow up period. This will require a parametric model. At each DSMB meeting we will report on the current estimate of  $p$ . If  $p$  is significantly ( $p=0.05$  one sided) less than 0.67 the DSMB may recommend that the trial no longer have survival as a primary endpoint and be redesigned to focus on ALSFRS-R measured for 12 months.

The justification of this target is as follows. If  $p=0.67$ , that is, a subject is on treatment for 67% of the time they are in the study, and  $R=2$  then  $1/(p/R+(1-p))=1.5$ , which means that subjects while being treated will survive for 1.5 times longer than untreated subjects. Thus an on-treatment hazard ratio of 2 would give an intent-to-treat hazard ratio of 1.5. We feel that an on-treatment hazard ratio of 2 is feasible but any higher hazard ratio is unlikely to be met, so our target for  $p$  will be set to 0.67, that is, all treated subjects would be required to remain on their treatment for at least 67% of the total time they are in the study.

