### ***Long Term Treatment with IV Ceftriaxone***

**Human Studies.** Several studies have been published on the use of ceftriaxone for longer than six weeks of treatment [111-118]. Frequently, patients receive multiple (up to five) courses of treatment. These published reports are specific to the treatment of Lyme disease and osteomyelitis. However, a growing number of patients with ALS are currently receiving chronic ceftriaxone treatment. Neither the published reports nor the direct communication with physicians treating patients with long-term ceftriaxone have reported any adverse events. The results of the published studies can be reviewed in the Clinical Investigator Brochure, section 5. Correspondence with physicians who treat Lyme disease has revealed gallstones and biliary sludging to occur in approximately 10% of treated patients (personal communication with [name], MD, [name], MD, [name], MD, [name], MD, and [name], MD from May to July, 2004). Those physicians that treat the cholelithiasis with deoxycholic acids have seen favorable results. No case of renal failure has been reported by these physicians.

The study DSMB reviewed unblinded safety and tolerability data from STAGE 1 and 2. Both 2 and 4 grams/day of ceftriaxone were tolerable at 20 weeks. In STAGES 1 and 2, the risk of symptomatic biliary events overall was 26%. Data from STAGES 1 and 2 suggested that ursodiol was helpful in management of cholelithiasis and biliary sludge events and was safe and well tolerated. Ursodiol did not have an effect on ceftriaxone blood levels.

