### **5.4.2 Dosage Suspension**

If an adverse event is serious or life threatening, the study drug should be suspended. Additionally, a “drug suspension” may occur at the Site Investigator’s discretion. The site will notify the Coordination Center within 24 hours of any dosage suspension.

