## **8. CRITERIA FOR INTERVENTION SUSPENSION, RECHALLENGE, OR PERMANENT DISCONTINUATION**

### **8.1 Intervention Suspension Related to Ceftriaxone Use**

**Study drug will be suspended under the following circumstances:**

(Please refer to the Manual of Operations for details regarding management of AEs)

- If the subject has *C. difficile* infection and is concurrently systemically ill with fever, leukocytosis or if the symptoms are refractory to treatment
- If the *C. difficile* infection results in pseudomembranous colitis
- If the subject is being treated for severe dehydration
- If the subject is symptomatic from biliary sludge
- If the subject is diagnosed with symptomatic cholelithiasis
- If the subject is diagnosed with invasive candidiasis
- If the subject is diagnosed with acute interstitial nephritis
- If the subject is diagnosed with acute tubular necrosis
- If the subject is diagnosed with renal failure
- If the serum creatinine doubles as compared to the screening visit value, the test will be repeated. If the value is confirmed (doubled as compared to screening visit value), study drug will be suspended while subject is evaluated.
- If the urinalysis is positive for Wright's or Hansel's stain as this is suggestive of eosinophiluria, or allergic interstitial nephritis
- If the spot urine protein is greater than 1000 mg. This is likely an indication of severe renal toxicity
- If the subject becomes oliguric, which is defined as urine output less than 500 mL/day. This can be an indication of severe renal toxicity
- If the Absolute Neutrophil Count (ANC) is less than 1.2 th/cmm

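### The on-treatment fraction p is defined as time on drug but estimated from a single-stop discontinuation curve, so suspended and restarted time is miscounted against the 0.67 target

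*Combined protocol and SAP*

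**What the plan says.** Under Treatment Discontinuation Rate Targets in Section 9.1.3 (Stopping for Futility in STAGE III), p is the ratio "of the follow up that a patient is on treatment divided by their total follow up". It links the on-treatment hazard ratio R to the intent-to-treat hazard ratio through 1/(p/R+(1-p)). With R = 2 and p = 0.67 the plan obtains 1.5. The choice of R is a judgement: "We feel that an on-treatment hazard ratio of 2 is feasible but any higher hazard ratio is unlikely to be met".

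The estimator is stated as follows: "The parameter $p$ will be estimated by the sum of the area under the time to discontinuation curves for each subject’s potential follow up", and this sum is "divided by the sum of the area under the time to death curve". A parametric model projects both beyond current follow-up. The current estimate goes to every DSMB meeting. If it is significantly below 0.67 (one-sided 0.05), the DSMB may recommend dropping survival as a primary endpoint.

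Sections 5.4.2, 5.4.3 and 5.4.4 treat suspension, re-challenge and permanent discontinuation as separate states, and give no maximum length for a suspension. Section 8.1 lists required suspensions, among them "If the subject is symptomatic from biliary sludge", and allows re-challenge after several of them. For Stages 1 and 2, Section 2.2.2 reports that "the risk of symptomatic biliary events overall was 26" percent. On reporting, Section 5.4.2 states: "The site will notify the Coordination Center within 24 hours of any dosage suspension". Section 5.4.3 requires notice before re-challenge.

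**The concern.** A time-to-event curve can record going off drug but not coming back on. The defined p and the hazard-ratio formula need actual time on drug. No section subtracts suspended time from the numerator, and Section 9.1.3 does not say which stop is the event.

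- **Event is permanent discontinuation** (the usage in Sections 5.4.4 and 6.2.3). Time in suspension, whether before a restart or before discontinuation is finally declared, counts as treated, and p is too high.
- **Event is the first stop of any kind.** All time after a restart counts as untreated, and p is too low for every subject who restarts.

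The result is compared with a threshold that bears on whether survival stays a primary endpoint. Under the first reading, a reported p near 0.67 can fail to prompt the recommendation although true exposure is below what the plan says is needed for an intent-to-treat hazard ratio of 1.5.

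**Working it through.** **The plan's own figure.** The intent-to-treat hazard ratio is 1/(p/R + 1 - p). With p = 0.67 and R = 2 this is 1/(0.335 + 0.33) = 1.504, and exactly 1.5 at p = 2/3. The arithmetic of the target is sound; the gap lies in how p is measured.

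**Baseline power.** Inputs from Section 9.1.3 are 243 to 293 events at month 39, 2:1 allocation and a final one-sided boundary of 0.019872 (z = 2.056). Power = Φ(ln(HR) × √(events × 2/9) - 2.056). At HR 1.504 this is 82.7% with 243 events and 89.2% with 293, in line with the plan's statement of over 80%.

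**Illustration.** The event is taken as permanent discontinuation. Assumptions not in the documents: 26% of treated subjects are suspended once, for w weeks on average, over 78 weeks of total follow-up. The 26% is the Stage 1-2 biliary figure carried forward. The 78 weeks is the 18-month average of Section 6.3.4. Mean suspended time per subject is 0.26w weeks, so true p = 0.67 - 0.26w/78.

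| w (weeks) | 0.26w/78 | True p | ITT hazard ratio (R = 2) | Power, 243-293 events |
|---|---|---|---|---|
| 0 | 0 | 0.670 | 1.504 | 83-89% |
| 4 | 0.013 | 0.657 | 1.489 | 81-88% |
| 8 | 0.027 | 0.643 | 1.474 | 79-86% |
| 12 | 0.040 | 0.630 | 1.460 | 77-84% |

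Section 6.3.4 describes the 18 months as on-treatment follow-up. If the 78 weeks is therefore read as time before discontinuation, the suspended share is s = 0.26w/78 of that time and true p = 0.67(1 - s). That gives 0.661 at 4 weeks and 0.643 at 12 weeks, a somewhat smaller error.

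**Effect on the rule.** Let s be the share of pre-discontinuation time spent suspended. The curve then reads true p/(1 - s). Assume a true p of 0.62 and s = 5%; the reported value is 0.62/0.95 = 0.653. The rule acts when the estimate is below 0.67 - 1.645 × SE. The documents give no standard error, so a range is shown.

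| Assumed SE of p | Chance the rule acts, s = 0 | Chance the rule acts, s = 5% |
|---|---|---|
| 0.015 | 95% | 31% |
| 0.02 | 80% | 22% |
| 0.03 | 51% | 14% |

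An s of 5% lies inside the illustration: with 0.67 × 78 = 52.3 pre-discontinuation weeks, 8 and 12 weeks of suspension give s = 2.08/52.3 = 4.0% and 3.12/52.3 = 6.0%.

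**The case against.** **Direction.** A reader might infer that p is simply inflated. The documents do not establish that, because Section 9.1.3 never defines the curve's event. Permanent stop is the natural reading from Sections 5.4.4 and 6.2.3. But Section 7 refers to Section 8 as discontinuation criteria although Section 8.1 lists suspensions open to re-challenge, and Section 7.3 speaks of drug being discontinued and later resumed. What stands is that neither reading matches the definition.

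**Size.** A reader might also infer that suspension will be common and the power loss large. The documents give no suspension frequency or length. The 26% predates routine ursodiol in Stage 3. Section 2.2.2 calls these events symptomatic, while Section 5.1.2 gives 26% as the overall biliary rate. Section 5.1.2 also credits dosage reduction, so not every event need have meant suspension. Anchoring power at exactly 80% would exaggerate the loss, since the plan's own events and boundary give 83-89%.

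**Role of p.** The plan calls this its simplest model and its hazard ratio approximate. Section 9.1.3 makes the DSMB action a possible recommendation, although its earlier paragraphs are worded more firmly. The worked example after the Feasibility/Futility table instead requires p to be significantly better than 67%. That conflicts with the rule above and must be reconciled. If it governs, its margin (1.645 × 0.02 = 0.033 at an SE of 0.02) exceeds the 4- and 8-week errors. An overstated p makes either version more lenient, but these points hold the matter to a moderate grade.

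**Remedy.** Dividing observed days on drug by observed days alive would be wrong under staggered entry. It over-weights early follow-up, when most subjects are still on drug. This objection stands, and the fix keeps the projection.

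**Conclusion.** The concern holds as a mismatch between a stated quantity and its stated estimator. It should be corrected, though the likely effect on power is modest. Under the permanent-stop reading, and assuming one 4- to 12-week suspension in 26% of subjects over 78 weeks, a reported 0.67 overstates p by about 0.01 to 0.04. The intent-to-treat hazard ratio is about 0.01 to 0.04 below 1.50, and survival power about 1 to 6 percentage points lower. The consequence for the rule can be larger when p is near the threshold, but that depends on an assumed standard error and an assumed true p. Suspension frequency and length in Stage 3 are unknown, and the error could be smaller than shown. Drug holidays are not part of the point: Section 5.1.3 justifies them by CSF levels staying above the criterion for at least 60 hours, so counting them as treated is defensible.

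**What to change.** In Section 9.1.3, under Treatment Discontinuation Rate Targets:

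1. Define the event of the time-to-discontinuation curve as permanent discontinuation.
2. Keep the curve-based parametric projection over each subject's potential follow-up.
3. Remove suspended time from the numerator, for example by multiplying the curve-based estimate by one minus the observed share of pre-discontinuation time spent in suspension, taken from recorded suspension and restart dates.
4. State that permitted drug holidays count as on treatment.
5. Show suspended time separately in each DSMB report.

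No clinical rule changes. The information is already gathered: suspensions are notified within 24 hours, re-challenge is notified beforehand, and syringes are counted at visits (Section 5.2.3). The cost is a revised paragraph, some DSMB report programming and a slightly lower p.
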